## Monitoring and data quality oversight

Given the observational, registry-based design of this study, a formal independent data monitoring committee is not required. Data quality will be overseen by the registry Director (HW) and the Study Coordinator. Routine data quality checks will be performed quarterly, including review of completeness, range checks, and cross-field consistency within REDCap. Any data queries will be resolved by the data abstractors in consultation with the clinical team. An annual internal audit of a random sample of records against source documents will be conducted to assess data accuracy. Audit findings, inter-abstractor reliability statistics, and the protocol adherence metrics described above will be summarised in an annual data quality report, reviewed by the COCOE steering group and retained for reporting to the MUHC REB.

## Protocol amendments

Any substantive amendments to this protocol, including changes to eligibility criteria, data collection instruments, or consent procedures, will be submitted to the MUHC REB for approval prior to implementation. Non-substantive administrative amendments will be documented in a protocol amendment log maintained by the Study Coordinator. All approved amendments will be reflected in an updated protocol version with a revised version number and date, and will be reported in any resulting publications.

## Ethnicity and cultural safety

This research may involve participants from First Nations, Inuit, and Métis communities. Following consultation with an Indigenous research advisor, a formal Cultural Safety Review was determined not required. The consultation concluded that the study design does not involve data collection specific to or within Indigenous communities, and that the scope and conduct of the registry do not meet the threshold requiring a formal Cultural Safety Review under current institutional guidelines. Ethnicity data will be collected solely for demographic description, using Statistics Canada Indigenous identity categories, with participants having the option to self-identify broadly as Indigenous, First Nations, Métis, or Inuit. No population-specific sub-analyses will be conducted and no identifiers linking participants to specific communities will appear in any analysis or publication output. The study team acknowledges that the area-level Pampalon MSDI, derived at the forward sortation area level, may not adequately capture the social and material circumstances of Indigenous participants in urban Montréal due to within-FSA heterogeneity; this is noted as a study limitation. Future iterations of the registry will consider engagement with urban Indigenous health organisations to inform culturally appropriate data collection.

## Patient and public involvement

To ensure patient-centred research, a Patient Partner Committee is being established with support from Unité de soutien SSA-Québec – RUISSS McGill. Patient partners will actively shape research priorities, refine study designs, interpret results, provide guidance on ethical considerations and knowledge translation strategies, and continuously disseminate findings within patient and social networks. This study follows the Strategy for Patient-Oriented Research (SPOR) patient engagement principles [44].

## Ethics and dissemination

### Ethics approval

This study is conducted in accordance with the Tri-Council Policy Statement: Ethical Conduct for Research Involving Humans (TCPS2) [23]. Ethics approval has been granted by the McGill University Health Centre Research Ethics Board (MUHC REB No. 2026–10997), which is responsible for monitoring the study at all participating institutions in the health and social services network in Québec. Authorisation to access patient charts is obtained from the Director of Professional Services (DPS). Access occurs only after consent has been obtained from the patient and family.

### Dissemination policy

Findings will be disseminated regardless of direction or magnitude of results.

### Confidentiality and data governance

All data collected from a participant are considered personal information and are kept confidential within the limits of the law. Upon enrollment, each participant is assigned a unique registry identifier known only to the principal investigator, co-investigators, and research assistants. Participant names do not appear on any data collection forms. Data within the registry are de-identified. The only protected health information collected includes dates (birth, discharge, death); for publication, dates are converted to relative units (e.g., days from birth), birth year is provided, and no centre identifiers are released.

The data registry is situated within and under the auspices of the MUHC Department of Paediatric Surgery. Electronic data are stored on password-protected computers in administrative offices. Paper records and signed consent forms are stored in a locked filing cabinet in a locked room. The REDCap server is located within the IT department of the Research Institute of the MUHC. Access to the registry is restricted to authorised personnel (the principal investigator (PI), co-principal investigators, and students/trainees granted explicit access). The master linking log is stored on a password-protected encrypted external USB drive kept in a locked cabinet in the principal investigator's office.

Participants may withdraw from the registry at any time by verbal or written request. Upon withdrawal, clinical data are destroyed and personal information deleted from paper and computer records. A confirmation letter is provided. Research results already obtained from analysis of registry data will not be destroyed and may be used for other research projects (subject to ethical approval).

The guardian of the data is the principal investigator, [name]. If [name] leaves the Montreal Children's Hospital, guardianship is transferred to the new principal investigator. The data will be stored for as long as the registry has scientific interest and the Director can ensure its management.

### Potential benefits and harms

There are no direct benefits to patients or caregivers from participating in this registry; however, participants may derive satisfaction from contributing to a national dataset that will improve understanding of colorectal disease management and outcomes. There are no known harms. The potential for privacy breach is minimised by strict confidentiality and de-identification protocols. Participants may have access to their research file to verify and correct their data. Third parties such as insurers or employers may not access registry data unless authorised by a court of law or by the person who contributed the data. Participants will not incur additional costs and will not receive compensation, though a certificate of participation is available upon request.

## Strengths and limitations

The principal strengths of the COCOE Registry are its prospective, longitudinal design with follow-up to age 18; its use of validated, age-stratified, disease-specific instruments administered in both official languages; its embedding within an established multidisciplinary clinical pathway rather than a parallel research process; and the pre-specification of outcomes, analyses, missing data handling, and adherence metrics before any analysis is conducted.

Several limitations follow directly from the design and should temper interpretation of registry outputs. The registry is single-centre. Although COCOE serves a wide provincial and inter-provincial catchment, its case-mix reflects a tertiary referral pathway and is likely to be enriched for complex, syndromic, and reoperative presentations relative to the population of all children born with HD or ARM in Canada. Families living at a distance from Montréal, families without stable housing or telephone contact, and families whose preferred language is neither French nor English are plausibly under-represented at both enrolment and follow-up; the resulting bias would favour better-resourced families with better measured outcomes, which is the direction that most threatens the validity of continence and quality-of-life estimates. Registry outputs should therefore be read as describing a referred paediatric colorectal population rather than as national incidence or outcome estimates, and comparisons with ARM-Net and PCPLC data should be made with case-mix in mind [11,13]. The registry infrastructure, data dictionary, and REDCap instruments have been deliberately designed to be transferable to additional Canadian centres, and multicentre expansion through CanCORPS is the primary planned mitigation.

Combining HD and ARM within a single registry carries both operational and analytic risks. Operationally, the two cohorts share only part of the data model. Shared elements (demographics, social determinants of health, health service utilisation, PedsQL modules, PECI, PREOM-BMP, TRAQ, and the loss-to-follow-up definition) are captured on common forms, while disease-specific elements (Krickenbeck classification and the BCS for ARM; length of aganglionosis, HAEC ascertainment, and the BFS for HD) are captured on separate branching instruments, so that no clinician or abstractor is presented with a field that does not apply to the patient in front of them. Analytically, the two cohorts are never pooled for primary, survival, or multivariable analysis, and the events-per-variable threshold is assessed within each cohort separately. This is a conservative choice that may delay adjusted analyses in the smaller HD cohort. Pooling is confined to descriptive summaries of registry-level metrics such as enrollment, data completeness, and loss to follow-up, where disease group will always be reported as a stratifying variable. The main residual risk is therefore loss of statistical efficiency rather than confounding, and it is accepted in preference to a single combined model whose coefficients would be difficult to interpret clinically.

Finally, the primary outcome relies on instruments administered by proxy in younger children and by self-report from age 12, so the change of respondent within an individual’s follow-up may introduce measurement discontinuity. Respondent type will be included as a covariate in longitudinal models, and the pre-specified landmark estimates at ages 5 and 10 fall wholly within the proxy-report period, allowing an interpretation that is unaffected by the transition to self-report.

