### Loss to Follow-Up

A participant will be considered lost to follow-up if there has been no clinic encounter, completed survey, or successful contact (by telephone, email, or mail) for 18 or more consecutive months in a participant aged under 18 years who has not yet transitioned to adult care or withdrawn from the registry.

When a participant misses a scheduled visit without prior notification, the research assistant will initiate a standardised re-contact sequence: (1) two phone call attempts within 2 weeks; (2) email or written letter within 4 weeks, if contact information is on file; and (3) two further phone call attempts at 3 months. If no successful contact is made after this full sequence, the participant will be flagged as lost to follow-up in REDCap with the date of last confirmed contact recorded. All contact attempts and outcomes will be logged prospectively.

Rates and timing will be reported descriptively at each annual analysis. In survival and longitudinal analyses, the loss will be treated as censoring at the date of last confirmed contact. The potential impact of informative (non-random) censoring will be examined using inverse probability weighting (IPW) as a sensitivity analysis [26,27]. Factors independently associated with the loss will be examined using logistic regression (ever-lost vs retained) as a secondary analysis, with candidate predictors pre-specified to include: diagnosis type, age at enrollment, sex, aganglionosis length or ARM Krickenbeck category, area-level deprivation quintile, and distance from COCOE.

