### Missing data

Missing data will be characterised in terms of amount and pattern at each planned analysis. For multivariable analyses, data missing at random (MAR) will be handled using multiple imputation by chained equations (MICE) with 20 imputed datasets pooled using Rubin's rules [42]. Complete-case analyses will serve as the primary approach and MICE results as sensitivity analyses. Where data missing not at random (MNAR) cannot be excluded (particularly for SDOH variables where “prefer not to answer” may be non-random), best-case and worst-case sensitivity analyses will be conducted [42].

Missing patient-reported outcome data and incomplete follow-up are anticipated to be the principal analytic challenges over the observation window to age 18, and are addressed by a pre-specified hierarchy of methods. At the item level, partially completed questionnaires will be prorated according to the developer’s published scoring rule, and scale scores will be set to missing where fewer than the minimum required items are available. At the visit level, longitudinal analyses of PRO scores will use linear mixed-effects models and generalised estimating equations, which retain participants with incomplete visit series and yield valid inference under a missing-at-random assumption [41]. For multivariable models requiring complete covariate vectors, multiple imputation by chained equations will be used, with the imputation model including the analysis model variables, the outcome, and auxiliary variables predictive of non-response (age band, distance from COCOE, deprivation quintile, language of administration, and number of previously missed appointments) [42].

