As loss to follow-up and PRO non-response may both be informative, inverse probability of censoring weights estimated from these same predictors will be applied as a sensitivity analysis to the survival and longitudinal models [26,27]. Robustness to departures from the missing-at-random assumption will be assessed using pattern-mixture models in which imputed PRO scores are delta-adjusted by 0.2, 0.5, and 0.8 standard deviations in the unfavourable direction. The amount and pattern of missingness, by instrument, visit, and disease cohort, will be tabulated in every registry publication, and no outcome analysis will be reported without the accompanying completeness figures. A pre-specified threshold of more than 40% missingness for a given instrument at a given assessment point will preclude model-based inference for that instrument at that point, which will instead be reported descriptively.

This protocol paper has additionally been prepared with reference to the SPIRIT 2025 statement (Standard Protocol Items: Recommendations for Interventional Trials) [43], adapted for observational registry protocols. A completed SPIRIT checklist is provided as S1 File.

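### The missing-not-at-random check shifts scores in one direction only and covers patient-reported scores only; the primary time-to-continence outcome has no clearly assigned counterpart

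*Protocol article*

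**What the plan says.** Four provisions in the protocol article bear on this.

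- **Patient-reported scores.** The Missing data section accepts that both loss to follow-up and questionnaire non-response may be informative. It then assesses robustness to departures from missing at random with "pattern-mixture models in which imputed PRO scores are delta-adjusted by 0.2, 0.5, and 0.8 standard deviations in the unfavourable direction". Size, sign and target are all fixed.
- **Time to continence.** Loss is censored at the last confirmed contact. Under Loss to Follow-Up, "The potential impact of informative (non-random) censoring will be examined using inverse probability weighting (IPW) as a sensitivity analysis". Missing data adds that "inverse probability of censoring weights estimated from these same predictors will be applied as a sensitivity analysis to the survival and longitudinal models". The list just before that sentence is age band, distance from the centre, deprivation quintile, language of administration and number of missed appointments.
- **Best and worst case.** "Where data missing not at random (MNAR) cannot be excluded", "best-case and worst-case sensitivity analyses will be conducted". The only variables named are the social determinants, introduced by the word particularly. Whether scores or continence times are included is not stated.
- **Direction of bias.** Strengths and limitations expects families who are remote, hard to contact or speak neither French nor English to be under-represented at enrolment and follow-up. The resulting bias favours better-resourced families with better measured outcomes, "which is the direction that most threatens the validity of continence and quality-of-life estimates".

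Table 2 also matters: the primary event is the first visit at which the threshold is met, confirmed at a subsequent visit.

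**The concern.** The stated aim is general, but only one sign is tested. If children who are doing well respond or attend less, their missing scores are better than the observed ones, and every unfavourable delta moves the estimate further from the truth.

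Several features make that direction plausible:

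- Clinic contact is partly driven by need. Patient-reported outcomes expects 40–50% of participants to be in a supervised bowel management programme at any assessment visit.
- The full survey set takes 54–95 minutes before staggering, and a family with few problems has less reason to complete it.
- The confirmation rule affects the primary outcome directly. A child continent at one visit who is lost before the next is censored rather than counted, which lowers the continence curve.
- Loss is material. About 3 of the 8 expected monthly enrolees are previously lost patients who have been re-engaged.

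For continence, weights built on the listed predictors correct for loss that those variables explain. They do not correct for loss that depends on how the child's bowel function is developing. The proportions continent by ages 5 and 10 are meant for benchmarking against published cohorts, so a result could be called robust without this departure having been examined.

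**Working it through.** The plan gives no figure for its own sensitivity range. Its one related projection, 145–240 continence events, reproduces (480 × 0.30 = 144; 680 × 0.35 = 238) and is not in dispute.

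**Mean scores**

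Inputs from the protocol: instrument completion of 70–80% per visit, hence 20–30% missing; a ceiling of 40% missing for model-based inference; deltas of 0.2, 0.5 and 0.8 SD. Assumed: non-responders are better by 0.5 SD.

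Shift in the overall mean = missing share × delta.

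| Missing | Planned deltas 0.2 / 0.5 / 0.8 SD | Truth if non-responders are 0.5 SD better |
|---|---|---|
| 20% | −0.04 / −0.10 / −0.16 SD | 0.20 × 0.5 = +0.10 SD |
| 30% | −0.06 / −0.15 / −0.24 SD | 0.30 × 0.5 = +0.15 SD |
| 40% | −0.08 / −0.20 / −0.32 SD | 0.40 × 0.5 = +0.20 SD |

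No planned delta gives an estimate above the missing-at-random value, so the truth in the last column lies outside the delta range in every row. With non-responders 0.2 to 0.8 SD better, the 30% row becomes +0.06 to +0.24 SD.

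For scale, the 95% half-width of a mean is about 1.96/√(n × share observed). With 30% missing:

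- n = 480: 1.96/√336 = 0.11 SD, smaller than 0.15.
- n = 150: 1.96/√105 = 0.19 SD, larger than 0.15.

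**Continence by age 10**

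All inputs here are assumptions: 33% continent by age 10 under independent censoring, constant hazard from age 3 (7 years), loss at a rate c of 0.05 or 0.08 per year, and a post-loss hazard r times the pre-loss hazard.

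- λ = −ln(0.67)/7 = 0.0572 per year.
- With a = λ + c − rλ, true proportion = 1 − [exp(−(λ+c)t) + c·exp(−rλt)·(1 − exp(−at))/a].
- For c = 0.05, r = 2, t = 7: a = −0.0072; first term exp(−0.7505) = 0.472; second term 0.05 × 0.449 × 7.18 = 0.161; result 1 − 0.633 = 36.7%.

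| Loss rate per year | r = 0.5 | r = 1 | r = 2 |
|---|---|---|---|
| 0.05 | 30.8% | 33.0% | 36.7% |
| 0.08 | 29.6% | 33.0% | 38.5% |

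A second set of assumptions starts from a curve at 30–35% with 20–40% lost over the period. A hazard ratio of 2 to 3 after loss puts the truth about 2 to 9 points higher (30% becomes 32.3% at the low end; 35% becomes 44.2% at the high end). If no lost child gains continence, 30% falls to 27.1%, 25.5% and 23.8% at 20%, 30% and 40% lost.

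**The case against.** The strongest reply is that the plan is less one-sided than the delta rule suggests, and much of it stands.

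- A reader might infer that the protocol assumes selective loss can only flatter results. It does not say so: it ranks that direction as the greatest threat, and nothing links that sentence to the sign of the delta. The limitations text needs no rewriting on this account.
- A reader might also take the statement that the clinic is "likely to be enriched for complex, syndromic, and reoperative presentations" as evidence that attendance rises with need. It concerns referral case-mix relative to all affected children in Canada, not who leaves after enrolment. No section states that children doing well drop out.
- The best-case and worst-case rule is not confined to social determinants. Since the plan concedes informative loss, its trigger is arguably met for outcomes. That leaves its scope unstated rather than settled.
- The continence curve does have an informative-censoring check, and the weights can move it either way, but only for loss explained by the predictors used. On the widest reading, the predictors could extend to other variables in the imputation model; naming the continence score would settle this.
- The continence instruments appear among the patient-reported surveys, so the deltas might reach them. But a shift in SD units does not by itself define a departure for a censored event time.
- Loss after confirmed continence does not affect the curve. Surveys can be completed between visits, and loss to follow-up needs 18 months without any contact, so a well child who attends less is not automatically lost.
- Some shifts lie within sampling error: 0.10–0.15 SD with 150 participants, or most of the continence shifts if each disease had about 240 children (half-width near 6 points at 33%). Bias does not shrink as the registry grows, however, while the interval does.
- An unfavourable-only delta is a recognised conservative choice, and a condensed article may leave detail to an analysis plan. Here, though, the sign and target are written down.

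**Conclusion.** The point holds in a limited form. The departure analysis is fixed in the unfavourable direction and for imputed patient-reported scores only, and no missing-not-at-random analysis is clearly assigned to time to continence.

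If non-responders do better, the true mean lies above every delta-adjusted estimate: by 0.10 to 0.15 SD at 20–30% missing and an assumed 0.5 SD, against a delta range of 0 to −0.16 or −0.24 SD. For continence, halving or doubling the post-loss hazard moves an assumed 33% to between 29.6% and 38.5%. The loss rates, the 0.5 SD and the hazard multipliers are assumptions; the documents give none of them.

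The documents do not support the stronger conclusion that the truth would lie outside everything reported. That is certain only for the delta range, because the best-case and worst-case analyses may cover outcomes. Nor is the primary outcome without any check. This is an inexpensive improvement to a stated rule, not a flaw that invalidates the analysis.

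**What to change.** In the Missing data section:

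1. Apply the 0.2, 0.5 and 0.8 SD deltas in both the unfavourable and the favourable direction.
2. For time to continence, add for each disease a sensitivity analysis in which the hazard after loss is multiplied by values on both sides of 1, for example 0.5 and 2. Report the age-5 and age-10 proportions under each.
3. Add the last observed continence score, where one exists, to the predictors of the censoring weights.
4. State whether the best-case and worst-case analyses cover patient-reported scores and continence as well as social determinants.

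Strengths and limitations can stay as written. No formal analysis has yet been conducted, so all of this can still be pre-specified. The cost is a few extra runs and a wider reported sensitivity range.
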